The core of PAL is that students acquire knowledge and skills through the active support of their peers [22]. The advantage of this model is transforming resource limitations into a teaching opportunity. By allowing students to act as facilitators, this approach greatly reduces the reliance on professional faculty. More importantly, it shifts students from being passive recipients of knowledge to active creators of it. In the process of teaching others, they can develop their leadership, communication, and organizational skills [23–25]. These are key competencies for their future careers that are difficult to achieve in traditional teacher-led models. Moreover, peer interaction can create a more equal learning environment [22]. This may help to increase student motivation and potentially reduce the learning burnout prevalent in nursing programs [26,27]. Previous studies show that student-led activities can effectively enhance professional identity [28–30]. Despite these advantages, the PAL model also faces its own challenges, such as a potential lack of student motivation or conflict within groups, as well as the need for structured training and resource support. All these factors must be considered in the design [31].

Therefore, this study aims to address the following research questions: (1) How was the student-led healthcare career experience activity developed? (2) How will the key outcomes (professional commitment, academic self-efficacy, and learning burnout) change across four measurement time points (T0-T3)? (3) What are the differences in outcomes between Group 1 at T1 and T2? (4) What are the differences in outcomes among all groups at T3?

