### 3.4. Sample size

The sample size was estimated specifically for a GEE analysis using the longpower package in R statistical software (version 4.4.3). The calculation was designed to detect significant differences in the primary outcome among the three groups across four repeated measurement points. The parameters were set based on standard benchmarks: a significance level (α) of 0.05, a power of 0.80, and a standard medium effect size (δ = 0.50). Regarding the correlation structure, we adopted a conservative estimation. Given that professional commitment is a dynamic construct [36], we assumed a moderate within-subject correlation (ρ = 0.35) [37]. Based on these parameters, the minimum required sample size is 33 participants per group. To account for a potential 10% attrition rate, the final target sample size is set at 110 participants. This method of ensuring adequate statistical power aligns with recommendations in methodological literature [38,39].

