### 3.8. Outcomes and measures

#### 3.8.1. Main outcome: professional commitment.

The primary outcome measure in this study is the change in professional commitment among nursing students. This outcome will be measured using the Undergraduate Professional Commitment Scale, developed by Lian R et al [42]. The scale is organized into four dimensions: emotional commitment, continuing commitment, ideal commitment, and normative commitment. It comprises 27 items, with responses rated on a 5-point Likert scale ranging from 1 (“completely inconsistent”) to 5 (“completely consistent”). Higher scores indicate greater professional commitment. The scale demonstrates strong reliability, with a Cronbach’s α coefficient of 0.927.

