### 3.9. Statistical analysis

All statistical analyses will be performed using SPSS version 27.0. Demographic variables will be summarized using descriptive statistics. In accordance with the Intention-to-Treat (ITT) principle, all randomized participants will be included in the analysis. Missing data will be handled using the GEE model under the Missing at Random (MAR) assumption. The GEE model will be used to compare differences between and within groups, controlling for time effects and baseline scores of the outcome variables (professional commitment, academic self-efficacy, and learning burnout). To examine the specific impact of each intervention role, the Group variable will be analyzed as a three-level categorical factor (Implementer, Observer, Waitlist). The interaction effect between time and group allocation will also be examined. Post-hoc multiple comparisons between groups will be conducted using the Bonferroni correction. For all analyses, statistical significance is set at a p-value of < 0.05.

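### No deciding contrast is fixed for professional commitment, and Bonferroni covers only between-group comparisons, so the chance of some false positive on the primary outcome is roughly 8% to 19%, depending on which tests count

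*Protocol article*

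**What the plan says.** Section 3.8.1 defines the primary outcome without a comparison: "The primary outcome measure in this study is the change in professional commitment among nursing students". No arms, visit or model term is attached.

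The Introduction poses three quantitative questions and ranks none of them. Research question 2 asks "How will the key outcomes (professional commitment, academic self-efficacy, and learning burnout) change across four measurement time points (T0-T3"). Questions 3 and 4, the second of which concerns the last visit (T3), continue: "3) What are the differences in outcomes between Group 1 at T1 and T2? (4) What are the differences in outcomes among all groups at".

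Section 3.9 adds a role factor with three levels (Implementer, Observer, Waitlist) in a GEE adjusted for baseline and time, and then a further test: "The interaction effect between time and group allocation will also be examined". Its error rules are: "Post-hoc multiple comparisons between groups will be conducted using the Bonferroni correction. For all analyses, statistical significance is set at a p-value of < 0.05".

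Section 3.4 plans the sample size with "a significance level (α) of 0.05, a power of 0.80, and a standard medium effect size (δ = 0.50") and, for the repeated measures, "we assumed a moderate within-subject correlation (ρ = 0.35"). It arrives at 33 per group, and 110 in total after 10% attrition.

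**The concern.** The tests bearing on professional commitment answer different questions and can disagree.

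- The role effect compares implementing with the control conditions.
- Research question 3 compares Group 1 just after implementing with the same students at follow-up, with no concurrent control.
- Research question 4 compares the groups at T3, when Table 3 shows that all three have already been implementers.
- The interaction asks whether the groups' time courses differ.

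Nothing in the document says which of these carries the trial's conclusion. The plan does address multiplicity, but its correction stops at between-group pairs, while every analysis is judged at 0.05. The role effect could be null while the interaction or the Group 1 comparison is significant, and the text would not prevent that result from being presented as an effect on the primary outcome. The choice has to be made before results are seen, because a later choice cannot restore the error rate.

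**Working it through.** **Inputs.** From section 3.4: α = 0.05 (sidedness not given, two-sided assumed), power 0.80, δ = 0.50, ρ = 0.35, 33 per group, four measurements. From section 3.9: Bonferroni for between-group comparisons, 0.05 for everything. From the Introduction: research questions 2 to 4.

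**1. The plan's own figure.** The two-group, time-averaged formula is n = 2(z₀.₉₇₅ + z₀.₈₀)²[1 + (m − 1)ρ]/(mδ²). With m = 4 this is 2 × (1.960 + 0.842)² × 2.05/(4 × 0.25) = 32.18, hence 33 per group. Then 3 × 33 = 99, and 99/0.90 = 110. Both stated figures are reproduced. They correspond to one unadjusted two-group difference averaged over four visits, which is none of the listed tests, so section 3.4 does not identify the deciding contrast either.

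**2. What Bonferroni does cover.** Three pairs, each at 0.05/3, give a familywise rate of 4.4%. Within its own family the correction works; any excess comes from the tests outside it.

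**3. Rough bound.** If tests were independent, k tests at 0.05 would give 1 − 0.95ᵏ: 9.8% for two, 14.3% for three, 18.5% for four.

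**4. Simulation under no effect and no time trend.** 20,000 runs, 33 per group, equal correlation 0.35 between visits. Role and between-group tests are baseline-adjusted, with Bonferroni over three pairs for roles and for the T3 comparison. Group 1 at T1 v T2 is unadjusted.

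| Tests counted on professional commitment | Chance of at least one false positive |
|---|---|
| Role pairs, interaction | 8.0% |
| Interaction, question 3, question 4 pairs | 12.2% |
| Role pairs, interaction, question 3, question 4 pairs | 14.9% |
| Same, with the overall role test in place of role pairs | 15.5% |
| Role pairs, interaction, questions 3 and 4, overall time test | 18.8% |

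Moving ρ from 0.2 to 0.7 changes each row by about one point or less.

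**5. Power of the candidate role contrasts.** These use a baseline-adjusted model with period effects, 33 per group, ρ = 0.35, δ = 0.50, and follow-up periods as a separate level. Power is Φ(δ/SE − z).

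- Implementer v Waitlist: SE 0.218. At two-sided 0.05, 0.50/0.218 − 1.960 = 0.334, power 63%. Across ρ from 0.2 to 0.5 it runs from 59% to 70%.
- Implementer v Observer: SE 0.145. At two-sided 0.05, 0.50/0.145 − 1.960 = 1.488, power 93%.

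The gap arises because, after baseline, Table 3 has a Waitlist cell only in Group 3 at T1. At Holm's first step (0.05/3, z = 2.394) the same arithmetic gives Φ(−0.100) = 46% and Φ(1.054) = 85%. Holm's later steps are less strict, so these are lower limits for each contrast.

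**The case against.** **The analysis plan may name the primary contrast.** A condensed article may leave this detail to a document not shown. That would dispose of a complaint about silence alone. Section 3.9, however, positively fixes the threshold for every analysis and the scope of the correction, and an analysis plan that ranked the tests would have to depart from that text. This part of the objection softens the point but does not remove it.

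**The plan never promises a 5% familywise rate.** This is correct. A reader might infer that the true error rate is some single figure near 15% against a promised 5%. The documents do not support that. The 0.05 is a per-test threshold and the sample-size α, and the total depends on which tests one counts and on treating any significant one as success, which the protocol does not say it will do.

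**Some listed tests are weak candidates.** The pairs in research question 4 are between-group comparisons and so are already Bonferroni-corrected; the simulation treats them that way. Section 3.9 treats time as something to control for, and a time trend is not an intervention claim, so the 18.8% row is the least natural reading. The interaction is worded as an addition. These points move the figure within the range, but even role pairs plus interaction exceeds 5%.

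**The three outcomes could be pooled.** A reader might multiply the problem across professional commitment, academic self-efficacy and learning burnout and quote a much larger rate. The abstract and section 3.8.2 label the latter two secondary, and research question 2's grouping of all three as key does not undo that. The pooled reading is not supported.

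**Conclusion.** The point holds in limited form. The document attaches no deciding contrast to its primary outcome, corrects only between-group comparisons, and judges everything else at 0.05. Under no effect, the chance of at least one false positive on professional commitment is roughly 8% to 19%, and about 15% when role pairs, the interaction, research question 3 and Bonferroni-corrected research question 4 all count.

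This rests on four assumptions: any one significant test would be reported as an effect; there is no true time trend (one would make within-group tests significant for reasons unrelated to the activity); tests are two-sided; and pairs are tested without first requiring a significant overall test, which would lower the between-group share. The result is insensitive to the within-student correlation. This should be corrected before results are seen; it is not a flaw in the design.

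**What to change.** In section 3.9, state that:

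- the one primary analysis is the baseline-adjusted role comparison (Implementer, Observer, Waitlist) on the professional commitment total score, with Holm across its three pairs at a two-sided familywise 0.05, and the trial's conclusion rests on it;
- the time-by-group interaction and research questions 2, 3 and 4 are exploratory, reported as estimates with 95% confidence intervals;
- academic self-efficacy and learning burnout are secondary and supportive.

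Section 3.8.1 should point to that comparison, and 3.9 should say how follow-up periods enter the three-level role factor.

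Do not make everything depend on Implementer v Waitlist first. At about 63% power, it would often block the better-powered Implementer v Observer comparison (about 93%).

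The cost is a few sentences, with no new data or visits. The price is that fewer results can be called confirmatory. The stated 80% power also needs checking against the chosen comparison: for the difference that section 3.4 appears to have sized, a correction over three pairs leaves 67% power at 33 per group, or needs 43 per group for 80%.

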### 3.10. Data sharing and dissemination

The reporting of the trial results will adhere to the consolidated standard of reporting trials (CONSORT) guidelines. Following the completion of data analysis, the findings are intended for publication in peer-reviewed journals and for presentation at academic conferences. The datasets generated from this study will be made available by the corresponding author upon reasonable request.

## 4. Discussion

This study protocol introduces a student-led healthcare career experience activity. The design integrates Life Cycle Theory for its structure and Kolb’s Experiential Learning Theory for its process. This PAL model aims to offer a sustainable solution to resource scarcity. It also helps student implementers bridge the gap between theory and practice.

A key strength of this study is its intervention design, grounded in Scaffolding Theory [45] and Social Cognitive Theory [46]. This framework is designed to support program sustainability while allowing for multi-dosage assessment. The proposed student-led model directly addresses the issue of resource scarcity in career experience activities [17,19]. Traditional programs depend heavily on continuous faculty input. In contrast, this model seeks to establish a self-sustaining cycle. Through the integration of vicarious experiences into the peer-assisted framework, the Observer phase is positioned as a necessary preparatory cognitive scaffold. In this mechanism, current implementers are expected to not only guide middle school participants but also implicitly train the observers. This process is anticipated to foster a system of autonomous operation, which has the potential to reduce the long-term demand on faculty and enhance scalability. Furthermore, treating the Observer as an active comparator allows for the examination of how different intervention dosages in an open-label setting might impact outcomes such as professional commitment.

Furthermore, the student-led approach transforms nursing students from passive learners into active practitioners. This is critical in a practice-oriented profession like nursing. Early practical application is essential for a smooth transition from student to professional [47–49]. Research also indicates that early exposure to the professional practice environment fosters a sense of belonging and confidence [50]. By providing an early practice scenario during the theoretical learning stage, this study serves to reinforce the nursing students’ future roles as nurses. Through repeated engagement in this practice, they can internalize their knowledge, thereby deepening their identification with the nursing profession and enhancing their professional commitment [51,52].

The methodological rigor in developing the intervention is another notable strength. The study applied Life Cycle Theory to systematically compile a list of nursing roles. This helps nursing students develop a more holistic understanding of the profession. In addition, a Modified Brainstorming Technique was used for the activity design. This structured approach ensured the scientific rationale of the intervention content. This development process offers a valuable reference for future researchers. By focusing on changes in professional commitment during this practice, the study also allows for a deeper understanding of Experiential Learning Theory.

Finally, the protocol incorporates several specific measures to control for potential biases, particularly those arising from the open-label design. The choice of a stepped-wedge, waitlist control design is itself a key bias-control strategy. This design ensures that all nursing students eventually receive the same intervention dosage, helping to reduce dose-response bias. It also helps minimize a uniform Hawthorne effect, as groups are in different roles at any given time. To further mitigate researcher and Hawthorne effects, the role of the research team members is strictly defined. They act only as coordinators and do not directly participate in the intervention activities, thus minimizing their influence on the nursing students. Furthermore, the protocol includes a direct check for the Hawthorne effect, the nursing students are asked in their growth files whether awareness of being studied affected their participation. To address outcome expectation bias, data is triangulated by comparing the quantitative results from questionnaires with qualitative insights from the nursing students’ reflections and feedback records. This mixed-methods approach enhances the overall credibility and reliability of the findings.

## 5. Limitations

Several limitations of this study protocol should be acknowledged. First, the follow-up period is short. Long-term outcomes, such as career retention after graduation, are not measured. Second, the outcomes rely exclusively on self-reported questionnaires, which may introduce social desirability or recall bias. Third, the study is conducted at a single college. This may limit the generalizability of the findings to other settings. Fourth, the trial is open-label, so blinding is not possible, and the potential for baseline imbalances remains. Finally, the use of a waitlist control group poses a risk. Participants might withdraw or seek other opportunities, which could lead to attrition or self-selection bias.

## 6. Implications

For practice, this student-led activity offers a feasible and low-cost model for the early cultivation of professional commitment. Nursing educators could integrate this activity into career planning courses. This would help nursing students better understand their future professional roles and reduce misconceptions. The model also fosters strong academic-practice partnerships. For future research, this study highlights several directions. Future work should use a longitudinal design to track long-term outcomes like career retention. Researchers could also incorporate more objective measures, such as academic performance records or feedback from supervisors. Finally, conducting multi-center trials is crucial to enhance the generalizability of the findings.

## 7. Conclusion

This study protocol details a structured, student-led healthcare career experience activity designed to enhance professional commitment among nursing students. The trial evaluates a peer-assisted learning model. It is expected to provide empirical evidence for a feasible and sustainable approach to career education. This approach also simultaneously addresses resource limitations. Ultimately, this research aims to inform the development of effective early career interventions to help stabilize the future nursing workforce.
